**Subjects are recruited for the trial by a pediatric emergency room nurse upon emergency room registration.** The emergency room nurses have previous experience of recruiting patients from two clinical trials. The subjects recruited to the study can also discuss the trial with the on-call physician. The subjects are asked to provide a written consent, after which they are randomized into groups in a 2:1 ratio (treatment under study:current treatment). The interventions are randomized by trial numbers and enclosed in non-transparent envelopes. After asking for consent, the nurse opens the envelope assigned to the number that tells which group the subject is assigned to. Patients randomized to the new treatment practice are asked to give a sample which is analyzed with the POC device in the emergency room. If there are technical problems with the analysis, the nurse may take a new sample if necessary; a note on the technical problem is entered in the device log. During the trial, the number of technical problems with analysis increased, and the device manufacturer was informed of all tests that had failed. During the trial, over a short period from Sep 8 to 28, 2019, an increase in the number of failed samples was observed (9 out of 56, i.e. 16% of all samples analyzed). According to the manufacturer, this was to a significant degree (4 out of 9, 45%) associated with problems with the sample cassette transportation chain and wrong storage temperature during transportation. As technical problems persisted, the operating system of the POC test device was updated on Jan 7, 2020.

If an unforeseen adverse event occurs during sampling, an adverse event report is recorded in the hospital's internal adverse event reporting system; in addition, the investigators are informed of the event. The POC test results are automatically recorded in Weblab and are thus available at the doctor's appointment. Samples are only taken at the on-call physician's discretion from the children randomized to the current treatment group. The samples are stored in the emergency room and transported to the laboratory for analysis at 7 am the next morning. The results are entered into Weblab in the microbiology lab, and the on-call physician is responsible for reporting the results and reacting to them.

Due to the SARS-CoV2 epidemic and change in testing practices, randomization was halted on March 13, 2020 at 3 pm when 1,350 subjects had been recruited.

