## Secondary outcome measures

- Treatment with antibiotics initiated within a week (7 days) of the emergency room visit and different groups of antibiotics
- Macrolide antibiotics prescribed in the ED
- Macrolide antibiotics started in infants under 3 months (proportion)
- Immediate admittance to hospital from emergency room (hospitalized pediatric patients)
- Pediatric patients admitted to hospital within a week (7 days) of the emergency room visit
- Diagnostic tests performed in the emergency room
- Outpatient phone contacts and their number (with nurse or physician) within 7 days
- Revisits to emergency room within the next 7 days
- Ancillary laboratory testing
- Intensive care or intensive monitoring within the next 30 days after the emergency room visit
- Mortality within the next 30 days after the emergency room visit
- Visit associated costs
- Length of stay at ED
- Pathogen directed therapy (defined as antimicrobial therapy directed against detected pathogen with specific treatment available)
- Time from emergency room visit to onset of pathogen-directed treatment

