**The randomization of patients was stopped on Mar 13, 2020 at 3 pm due to the SARS-CoV2 pandemic.**

#### 4.9. Statistical methods

The subjects are analyzed in the groups (*intention to treat*) they were randomized into. In the case of failure to comply with the study protocol, a secondary analysis is performed where the subjects are grouped according to the implemented intervention (*per protocol*). The proportion of children with an antibiotic prescription in the ED is reported separately for untargeted and pathogen-targeted antibiotic therapy.

If the POC test result is available for less than 70% of the patients randomized to the rapid group at the moment of decision-making, a separate per protocol analysis is done on the patients for whom the test result was available.

The statistical significance of the primary outcome measure is analyzed with SND (standard normal deviation) test. The difference between proportions is compared using the SND test, and 95% CI is reported for the differences between the proportions. Continuous outcomes (length of emergency

room stay, difference between cost of treatment) is analyzed using t test and 95% CI is reported. An alpha-error level of 5% (0.05) is used as cut-off value for P. New emergency room visits and hospital admissions are analyzed with Kaplan-Meier method using time-to-event analysis.

Of group demographic variables, means and standard deviations are reported when describing the patient material. As the differences between the groups are coincidental they are not tested statistically.

The Study Design section is written using the CONSORT 2010 checklist. The Ethics Committee of the Northern Ostrobothnia Hospital District gave a favorable opinion on the study protocol on Mar 20, 2019. On Apr 1, 2020, the Northern Ostrobothnia Hospital District granted permission for the trial comparing treatment methods. The trial was registered in clinicaltrials.gov on Apr 18, 2019. Recruitment of subjects commenced on May 6, 2019. Randomization was discontinued on Mar 13, 2020 due to the pandemic.

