| 

• Influenzavirus

➔ Start oseltamivir

• Mycoplasma pneumoniae

➔ >Start macrolide antibiotic

• Bordetella pertussis

➔ Start macrolide antibiotic

• Adenovirus with tonsillitis and high c-reactive protein

➔ Generally antibiotics are not useful

• Human metapneumovirus, Parainfluenza virus, Coronavirus, RSV

➔ Supports the clinical diagnosis of a viral infection

• Bocavirus

➔ Consider course of illness: wheezing mainly indicates viral etiology

• Picornavirus (Enterovirus or Rhinovirus)

➔ Consider investigating enterovirus PCR if infant and severe course of illness

➔ Consider c-reactive protein and possible coinfection with S. pneumoniae

 | 

• Mycoplasma pneumoniae

➔ Usually no macrolide antibiotics

• Bordetella pertussis

➔ Usually no macrolide antibiotic

 
For all pathogens: Consider the general condition of the patient and the level of c-reactive protein in the clinical decision making
 |

479

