## 2.6 Definitions of primary and secondary outcomes

### 2.6.1. Primary outcome

1. Proportion of children with antibiotic prescription at emergency room
2. The pathogen-targeted antibiotic therapy is defined as antibiotic therapy (not including antivirals) prescribed to a participant in whom pathogen with specific treatment available (*M. pneumoniae*, *L. pneumophila* or *B. pertussis*) was detected.

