| 7  | Revisits to emergency room within the next 7 days                                      | Proportion of children admitted to hospital or revisit at emergency room within 7 days after study entry                      |
| 8  | Outpatient phone contacts and their number (with nurse or physician) within 7 days     | Proportion of children with outpatient telephone contact within 7 days after discharge from emergency room                    |
| 9  | Ancillary laboratory testing                                                           | Number of diagnostic tests per child other than point-of-care test performed within one week                                  |
| 10 | Intensive care                                                                         | Proportion of children with admission to pediatric intensive care unit or intensive care unit within 7 days after study entry |
| 11 | Mortality within the next 30 days after the emergency room visit                       | Proportion of children who died within one month after study entry                                                            |
| 12 | Visit associated costs                                                                 | Cost in euros per child per visits                                                                                            |
| 13 | Length of stay at ED                                                                   | Length of stay at emergency room in minutes                                                                                   |
| 14 | Pathogen directed therapy                                                              | Proportion of children receiving correct pathogen directed therapy                                                            |
| 15 | Time from emergency room visit to onset of pathogen-directed treatment                 | Time to initiation of correct pathogen directed therapy                                                                       |

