#### **5.2.14. Proportion of children receiving correct pathogen directed therapy**

This outcome will be defined as proportion of participants with pathogen targeted treatment available in each randomization arm. The counts and proportions of participants in whom the pathogen with targeted treatment available was detected in each randomization arm will be reported. To analyze the outcome, we will calculate 95 % confidence intervals (CI) of the differences using a Standard Normal Deviate (SND) test for the proportions. Risk ratios (RR) with 95 % CI are calculated.

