#### **5.2.15. Time to initiation of correct pathogen directed therapy**

This outcome is defined as time to initiation of targeted antimicrobials. This outcome is analyzed with Kaplan-Meier method using time-to-event analysis with 95 % confidence interval reported. .

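### The SAP's definition of pathogen-targeted antibiotic therapy omits the drug-match condition that protocol 4.6 contains, so a non-matching antibiotic can be coded as targeted

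*Combined protocol and SAP*

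**What the plan says.** Protocol 4.9 divides the primary proportion: "The proportion of children with an antibiotic prescription in the ED is reported separately for untargeted and pathogen-targeted antibiotic therapy". The protocol does not define the two categories there. Its nearest definition is in the list of secondary outcomes in 4.6, where pathogen directed therapy is "defined as antimicrobial therapy directed against detected pathogen with specific treatment available".

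The SAP defines the category in 2.6.1 item 2: "The pathogen-targeted antibiotic therapy is defined as antibiotic therapy (not including antivirals) prescribed to a participant in whom pathogen with specific treatment available", followed by the three bacteria, was detected.

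Three other places in the SAP use the same idea:

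- 2.6.2, row 14, labels the outcome "Proportion of children receiving correct pathogen directed therapy" and gives no rule for what is correct.
- 5.2.14 makes that outcome operational as follows: "This outcome will be defined as proportion of participants with pathogen targeted treatment available in each randomization arm".
- 5.2.15 says: "This outcome is defined as time to initiation of targeted antimicrobials".

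The only drug-pathogen link in the documents is the physicians' guide in protocol Appendix 1. It has "Start macrolide antibiotic" against both M. pneumoniae and B. pertussis, and it has no entry for L. pneumophila.

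**The concern.** The split in protocol 4.9 is there to show whether prescribing moves from untargeted to targeted when a result is available. That reading needs the targeted category to hold drugs aimed at the organism found. Under SAP 2.6.1 item 2 a child enters the category on two facts, a listed bacterium detected and some antibiotic prescribed, even when the drug was chosen for something else.

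At stake are the two parts of the split and the consistency of outcomes 14 and 15. As written, the protocol and SAP would let two coders classify the same child differently. The SAP introduction says that the SAP is based on the latest protocol. The amendment list dates the current 4.6 wording to Mar 29, 2022, which is also the date of SAP version 7.0, so the two texts were meant to agree.

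**Working it through.** **Step 1: definitions side by side.**

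| Place | Must the drug match the pathogen? | Must the result come first? |
|---|---|---|
| Protocol 4.6, pathogen directed therapy | Yes | Not stated |
| SAP 2.6.1 item 2, targeted antibiotic therapy | No | Not stated |
| SAP 2.6.2 row 14 | Implied by the label, no rule | Not stated |
| SAP 5.2.14 | No; counts children for whom a targeted treatment exists | Not stated |
| SAP 5.2.15 | Not stated | Not stated |

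The drug condition is where protocol and SAP differ. Both are silent on timing.

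**Step 2: one child under each rule.** M. pneumoniae is detected and the child receives only a beta-lactam, for another diagnosis. Under the 4.6 wording, read with Appendix 1, the drug is not directed against the detected organism, so it is untargeted. Under SAP 2.6.1 item 2 both conditions are met, so it is targeted.

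**Step 3: effect on the reported proportions.** Let A be the proportion with any ED antibiotic, T targeted and U untargeted, each child counted once, so A = T + U. If a proportion m is miscoded, the report shows T + m and U − m. Their sum is still A, so the primary comparison does not change.

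**Step 4: size, as illustration only.** There is no figure in the plan to reproduce.

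From the documents:

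- 1,350 recruited (protocol 4.5) at 2:1, so 1,350 × 2/3 = 900 POC and 450 control children.
- Pooled antibiotic rate 30.4% (SAP 2.8).

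Assumed, because the documents give none of these:

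- 1% to 5% of tested children positive for one of the three bacteria.
- All POC children and 10% to 50% of controls tested.
- Positive children receive antibiotics at the pooled rate.
- 10% to 50% of those antibiotics do not match.

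Children with a detection and an antibiotic = N × share tested × positivity × 0.304:

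- POC: 900 × 1 × 0.01 × 0.304 = 2.7, up to 900 × 1 × 0.05 × 0.304 = 13.7.
- Control: 450 × 0.10 × 0.01 × 0.304 = 0.14, up to 450 × 0.50 × 0.05 × 0.304 = 3.4.

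Of these, miscoded:

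- POC: 2.7 × 0.10 = 0.3, up to 13.7 × 0.50 = 6.8 children, which is 0.03% to 0.76% of 900.
- Control: 0.14 × 0.10 = 0.01, up to 3.4 × 0.50 = 1.7 children, which is 0.003% to 0.38% of 450.

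If every such antibiotic were non-matching, the POC figure would be 13.7 children, or 1.52%. Prescriptions written because of the result would add to the antibiotic rate in positive children, but they should mostly match and so would not be miscoded.

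**The case against.** **The split is secondary.** SAP 5.1 plans its interval and risk ratio on any ED antibiotic and names no between-arm test of the split. This stands, and it limits the weight of the point.

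**The two definitions serve different outcomes.** SAP 2.6.1 item 2 concerns antibiotics under the primary outcome; protocol 4.6 concerns a secondary outcome. This is true on the page. But SAP 5.2.14 describes the pathogen directed outcome in terms of targeted treatment, so the plan treats the terms as one concept.

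**Drug class stays visible elsewhere.** Macrolides in the ED are a separate outcome, and antibiotic groups are reported at 7 days. This helps only in part, because neither is tied to detection.

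**Appendix 1 cannot be the coding key.** Protocol 4.5 presents it as a rough guide, and L. pneumophila is missing. This stands, and is why a separate list is needed.

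**Stronger readings that a reader might infer:**

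- *An antibiotic should count only if the result came first.* Protocol 4.6 does not say so. For control samples, protocol 4.5 states: "The samples are stored in the emergency room and transported to the laboratory for analysis at 7 am the next morning". The panel covering mycoplasma and pertussis runs in office hours. A result-first condition would therefore push targeted ED antibiotics in controls towards zero by design, and in 5.2.15 it would drop early matching treatment as an event.
- *Empirical treatment in controls gives near-zero times in 5.2.15 and hides the speed gain.* That section does not cite 2.6.1 and concerns antimicrobials generally; SAP 2.2.2 includes influenza among the targets. POC samples are taken at registration, so the assay time overlaps the wait for the physician. The documents allow no calculation of such an effect.

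**Conclusion.** The point holds as a wording conflict on drug match between SAP 2.6.1 item 2 and protocol 4.6. It affects the targeted and untargeted parts of the split and leaves outcomes 14 and 15 without a usable rule. It does not affect the primary comparison.

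The number of children miscoded cannot be derived from the documents. It is probably small: protocol 3.1 describes atypical pathogens as uncommon in Finnish data, and the illustration gives at most about 7 POC children with up to half of the antibiotics non-matching. That rests on the assumed positivity, control testing and mismatch shares, and on positive children receiving antibiotics at the pooled rate.

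Two inferences about size go too far. With 6% positivity, all positives treated and half of the antibiotics non-matching, one reaches 0.06 × 1.00 × 0.50 = 3.0 percentage points, which a reader might set beside the planned fall of 8 points (33% to 25%). Every input there is an assumed extreme, and the 8 points concern total antibiotics, which relabelling cannot change. A reader might also note that, if results changed no prescribing, testing all POC children but 10% to 50% of controls gives a spurious risk ratio for targeted therapy of 1/0.50 = 2 to 1/0.10 = 10. That ratio comes from unequal testing; a drug-match condition would not remove it.

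**What to change.** 1. Reconcile SAP 2.6.1 item 2 with protocol 4.6. Count an antibiotic as pathogen-targeted only if a listed pathogen was detected and the drug's class is one that the trial's clinicians have listed in advance as directed against that pathogen. Code every other antibiotic as untargeted, and state how a child given both kinds is counted.
2. Use the same drug-match definition for outcomes 14 and 15, with the list extended to the antimicrobials those outcomes cover. Reword SAP 5.2.14 so that it counts therapy received, as its heading says, and report detection of a treatable pathogen separately, as SAP 2.2.2 already does.
3. Have the sponsor reconcile L. pneumophila, which is in the SAP definition but absent from Appendix 1, before any such case is coded.
4. Do not make result-before-prescription part of the definition. Report, by arm, matching prescriptions made before and after the result was available as separate descriptive rows.

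The cost is a few lines of SAP text and recoding of a small number of pathogen-positive records. Under SAP 2.10 study physicians already review prescriptions by hand, and under protocol 4.5 results are held in Weblab. The descriptive rows also need the order of prescription and result for these records. The targeted proportion becomes slightly smaller.

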546 **Due to Covid-19 pandemic**, in mid-February 2020, we re-evaluated the statistical power to decide  
547 whether we will complete or discontinue the study if the Covid-19 pandemic will make the  
548 recruitment impossible. Based on the calculation, the sample size reached was considered sufficient  
549 in terms of statistical power even if the randomization had to be stopped prematurely due to Covid-  
550 19 pandemic.

551

552 *Version 8, Mar 16, 2020*

- 553 • A reference to termination of randomization was added to Section 4.8: The randomization of  
554 patients was stopped on Mar 13, 2020 at 3 pm due to the SARS-CoV2 pandemic.

555

556 *Version 9, Jan 7, 2021*

557

- 558 • **A summary tables of full updated literature review** are attached

559

560 *Version 10, Sep 7, 2021*

561

562 Addition to 4.9. *Statistical methods*:

563 “The proportion of children with an antibiotic prescription in the ED is reported separately for  
564 untargeted and pathogen-targeted antibiotic therapy.”

565

566 *Version 11, Mar 29, 2022*

567

568 Addition to 4.6. *Outcome measures*

569 *The definition for “Pathogen directed therapy”* has been specified as follows:

570 “defined as antimicrobial therapy directed against detected pathogen with specific treatment  
571 available”

572

573

574 **Table 1. Studies on clinical impact of point-of-care diagnostics of respiratory pathogens in acutely ill children with respiratory symptoms: study**  
 575 **design, sample sizes, methods and tested pathogens.**

| Study                                   | Study design                                                                                           | Sample size | Age                                                                                                   | Method                                                  | Pathogens tested | Results available (min) | Results available prior to ED visit |
|-----------------------------------------|--------------------------------------------------------------------------------------------------------|-------------|-------------------------------------------------------------------------------------------------------|---------------------------------------------------------|------------------|-------------------------|-------------------------------------|

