#### 2.5.1. Point-of-care test group (intervention group)

*The new treatment practice studied: **On emergency room registration, a sample is taken from children with respiratory tract symptoms and/or fever. The sample is analyzed with the POC device in the emergency room, and the result is available during the emergency room visit.***

- The sampling technique does not differ from the current practice and the sample is taken from phlegm suctioned from the patient or from the nasopharynx using a nylon or dacron swab in children with runny noses, and in unclear cases (fever with no respiratory tract symptoms), from the pharynx.

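### The targeted/untargeted split placed under the primary outcome depends on detection that is systematic only in the POC arm; it should be labelled as added after recruitment and reported descriptively

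*Combined protocol and SAP*

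**What the plan says.** Protocol 4.6 gives one primary outcome. SAP 2.6.1 lists two numbered items under that heading. Item 1 is "Proportion of children with antibiotic prescription at emergency room". Item 2 reads "The pathogen-targeted antibiotic therapy is defined as antibiotic therapy (not including antivirals) prescribed to a participant in whom pathogen with specific treatment available" was detected, and names *M. pneumoniae*, *L. pneumophila* and *B. pertussis*. Protocol 4.9 adds: "The proportion of children with an antibiotic prescription in the ED is reported separately for untargeted and pathogen-targeted antibiotic therapy". The amendment log dates that sentence to "Version 10, Sep 7, 2021". Recruitment had ended well before: "randomization was halted on March 13, 2020 at 3 pm when 1,350 subjects had been recruited" (protocol 4.5).

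Testing differs by arm. In the POC arm, at registration, "a sample is taken from children with respiratory tract symptoms and/or fever" (SAP 2.5.1), and the result is meant to be available during the visit. For controls, protocol 4.5 says: "Samples are only taken at the on-call physician's discretion from the children randomized to the current treatment group". Their stored samples go to the laboratory the next morning. The 2–3 hour control test covers influenza and RSV only, so it can detect none of the three listed bacteria. The wider control panel is run in office hours (SAP 2.5.2).

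SAP 5 promises pairwise comparisons between arms for each outcome. SAP 2.6.3, which holds the post hoc analyses, does not mention the split.

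**The concern.** A prescription is classed as targeted only if a listed bacterium was found, and whether it is found depends on the allocated arm. Take two identical children carrying mycoplasma, each given the same antibiotic in the ED. The POC child is normally counted as targeted. The control child is counted as untargeted unless the physician chose to send a sample. Randomisation balances carriage and prescribing, but it cannot balance a classification rule that is itself part of the intervention.

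Item 2 gives no time window for detection and no rule for untested controls. The definition is also looser than the one for pathogen-directed therapy in protocol 4.6. The SAP item counts any antibiotic given to a detected case, whereas the protocol requires treatment aimed at the detected pathogen.

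The split sits at primary level with no label showing that it came late. A shift in how prescriptions are classified could then be read as a change in prescribing, in an open trial whose overall primary result might show none.

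**Working it through.** **1. The plan's own figure.** The sample size in SAP 2.8 covers only the undivided outcome. With control n, POC 2n, r = 2, p_c = 0.33, p_t = 0.25, d = 0.08, p̄ = (0.33 + 2 × 0.25)/3 = 0.2767:

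n = [1.96 √(3 p̄(1−p̄)) + 0.842 √(2 p_c(1−p_c) + p_t(1−p_t))]² / (2d²) = 373.5

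The continuity correction gives (n/4)[1 + √(1 + 6/(2nd))]² = 392.0 controls and 784.1 POC. The plan states 373 and 747 uncorrected, and 392 and 785 corrected. It reproduces apart from rounding and is not in dispute. No power statement covers the split.

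**2. Dates.** Mar 13, 2020 to Sep 7, 2021 is 543 days; 543/30.44 = 17.8 months. This dates the protocol sentence only. The SAP's document history has no September 2021 version. Its only version after February 2020 is 7.0 (Mar 29, 2022), whose comment mentions the post hoc analyses requested in review and not item 2.

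**3. Shift with no effect on prescribing.** Let P be the proportion prescribed an antibiotic in the ED (equal in both arms), x the proportion of all children who are prescribed an antibiotic and carry a listed bacterium, and a the share of those carriers detected. Then targeted = x·a and untargeted = P − x·a. The spurious difference in untargeted use is −x(a_POC − a_control), which lowers untargeted use under POC whenever detection is higher there.

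Inputs:
- P = 31%, the 2015 sample in protocol 4.7 (the trial database showed 30.4% pooled in February 2020).
- 900 and 450 children: the 1,350 recruited, divided 2:1.
- a = 90% (POC) and 20% (control): **assumed**.
- x = 1%, 3%, 5%: **assumed**.

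z = (p₁ − p₂)/√(p̄(1−p̄)(1/900 + 1/450)), with p̄ the pooled proportion.

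| x | Untargeted, POC vs control | RR | z | Targeted, POC vs control | RR | z |
|---|---|---|---|---|---|---|
| 1% | 30.1% vs 30.8% | 0.98 | −0.26 | 0.9% vs 0.2% | 4.5 | 1.5 |
| 3% | 28.3% vs 30.4% | 0.93 | −0.80 | 2.7% vs 0.6% | 4.5 | 2.6 |
| 5% | 26.5% vs 30.0% | 0.88 | −1.36 | 4.5% vs 1.0% | 4.5 | 3.4 |

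Worked row, x = 3%: untargeted is 0.31 − 0.03 × 0.9 = 0.283 against 0.31 − 0.03 × 0.2 = 0.304, with pooled 0.290, so z = −0.021/0.0262 = −0.80.

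The targeted ratio equals a_POC/a_control = 0.9/0.2 whatever x is. At x = 1% the expected targeted counts are about 8 and 1, so that z is only approximate.

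**4. Sensitivity to POC failures.** With 70% detection in the POC arm and x = 3%, untargeted is 28.9% vs 30.4% (RR 0.95) and the targeted ratio is 0.7/0.2 = 3.5.

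**The case against.** The strongest reply is that item 2 is a definition. It stands in a section of definitions and names no proportion or comparison, and protocol 4.9 only promises separate reporting. A reader might infer from the plural "primary outcomes" in SAP 5.1 that the split has its own SND test and risk ratio. The documents do not support that: SAP 5.1 describes only overall ED prescribing, and the same sentence is repeated under two secondary outcomes (5.2.1 and 5.2.2). This part of the reply stands. Even so, SAP 5 calls for pairwise comparisons for each outcome and does not exempt item 2.

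A reader might also infer that a null primary result could become a significant fall in untargeted prescribing through classification alone. In the scenarios above the expected untargeted z never exceeds 1.36 in size. Protocol 3.1 describes atypical pathogens as uncommon in Finnish data, which favours the low values of x.

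Nor does every POC child get a result. Protocol 4.5 records device failures, SAP 4.4 lists missing samples as violations, and protocol 4.9 provides for results being available in fewer than 70%. In controls, detection is selective and late, not absent.

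Finally, earlier detection is how the intervention is meant to work, and time to pathogen-directed treatment was added on Feb 12, 2020, before randomisation stopped. That justifies reporting targeted therapy as a secondary outcome. It does not make the split a fair comparison of prescribing.

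**Conclusion.** The point holds, as something that should be fixed. The classification depends on allocation, the protocol sentence is late, and nothing where the split stands says so. The direction of the shift follows from the definition whenever detection is higher in the POC arm. Its size depends on carriage and detection shares that the documents do not give. On the assumed values the shift is modest for untargeted therapy and large for the targeted ratio.

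Two stronger conclusions should be avoided. The documents do not show that the SAP item was written on Sep 7, 2021; its date is unknown. They also do not show that the primary analysis is biased. The undivided intention-to-treat proportion, its test and its sample size do not use the split and are unaffected.

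**What to change.** - In SAP 2.6.1, state item 1 as the sole primary outcome.
- Move the split to SAP 2.6.3, labelled and dated as added after recruitment, and record when the SAP item was introduced. Mark the sentence in protocol 4.9 in the same way.
- Report targeted and untargeted counts descriptively by arm, with the number of children tested and the timing of results. State that a between-arm difference cannot be read as an effect on prescribing.
- Align the SAP definition with protocol 4.6, which requires therapy directed at the detected pathogen.
- Apply the same caveat to SAP 5.2.14, where proportions that depend on detection are explicitly compared with SND and RR.
- For a between-arm comparison whose classification does not depend on detection, rely on macrolide prescribing in the ED, which is already secondary outcome 2.

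The cost is wording in both documents and the loss of any between-arm claim about untargeted therapy. No new data on prescribing are needed; the testing counts and result times should come from laboratory records.
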